## Abstract

**Background:**

Falls are a major health care concern for our aging population. Previous research has identified impaired sustained attention as a risk factor for falls. Recently, meditation has been shown to improve different types of attention in various populations. However, there are no studies to date examining whether meditation training can improve sustained attention and mobility in older adults.

**Methods:**

We are conducting a 4-week proof-of-concept meditation intervention. We will recruit community-dwelling older adults. Participants will be randomized into one of two groups: (1) meditation training or (2) music listening (control). All participants will complete three 20-min group sessions per week and will be encouraged to continue their practice independently on the remaining days each week. Our primary outcome measure is behavioral performance on the Sustained Attention to Response Task (SART). Our secondary and tertiary outcomes include electroencephalograms (EEG) to assess attention and cognitive processing, mobility, and executive function.

**Discussion:**

Our proof-of-concept intervention aims to examine whether meditation training can improve sustained attention in older adults, who are known to be susceptible to falls. Importantly, our research has the potential to inform future clinical trials aimed at improving mobility and reducing falls risk in our aging population.

**Trial registration:**

Clinicaltrials.gov ID NCT03417635.

## Background

Approximately 30% of community-dwelling older adults experience one or more falls per year, resulting in injuries, loss of independence, and reduced quality of life. While there are known physiological risk factors for falls, including poor balance and altered gait patterns, it is now recognized that impaired cognitive functioning is also a risk factor for falls [1, 2].

Within the broad construct of cognition, one specific domain that has been focused on in the falls literature is attention [3, 4]. Anecdotally, older adults often cite the reason for their fall as “I wasn’t paying attention.” Empirically, the relationship between attention and falls has been tested using various measures of attention, including those examining divided [5, 6], visual-spatial [7, 8], and sustained attention [9]. Particularly relevant for our current study, we previously demonstrated that the number of falls experienced over a 12-month period was negatively associated with sustained attention based on reduced performance on the Sustained Attention to Response Task (SART) [9]. The SART requires participants to respond to frequently presented targets while withholding their response to infrequent targets. Because responses are frequent and repetitive, it is easy to make errors if you are unable to continuously maintain your attention to the task. Our previous findings corroborate research implicating sustained attention in postural control; indeed, completing a sustained attention task has been shown to impair subsequent performance on a postural control task [10].

Given the importance of sustained attention for postural control, improving attention in those at-risk for falls may improve their mobility and hence reduce their falls risk. One strategy that has been previously shown to improve attention is meditation. Meditation refers to a mental practice with the goal of strengthening one’s ability to focus attention for extended periods of time [11]. There are many cited physiological, cognitive, and psychological benefits of meditation, including regulation of the stress response in humans [12], changes in brain activity [13, 14], and reductions in depressive and anxiety symptoms [15]. Importantly, there is evidence that meditation can improve attention and executive functioning in healthy young adults [14, 16, 17]. For example, one study found that participants who completed a daily meditation practice showed improved attention in just 4 days [18]. More recently, researchers have replicated these findings in healthy older adults, who significantly improved their performance on an emotional-counting Stroop task measuring attention [19]. There have also been studies that have suggested that a consistent meditation practice can act as a neuroprotective agent against cognitive decline that is typical with aging [20].

There is also emerging evidence that meditation can change electrical activity in the brain, as measured using electroencephalography (EEG). In a systematic review [21], it was found that studies looking at EEG and meditation showed an increase in alpha activity during meditation, as well as increases in P300 event-related potential (ERP) component amplitude during various attention tasks, including a Go/No go task similar to the SART. Both alpha activity and P300 amplitude are modulated by attention. Collectively, these findings have been interpreted as showing that meditation can effectively change the electrical activity in the brain to increase attentional resources.

Our proof-of-concept study aims to investigate the impact of meditation training on measures of attention and corresponding electrical signals in the brain recorded using electroencephalograms (EEG) in older adults. More specifically, we are measuring continuous EEG during resting-state (i.e., the absence of an external task) which allows us to examine alpha activity. In addition, we are measuring ERPs during the SART. ERPs can be defined as time-locked recordings of brain activity corresponding to the presentation of stimuli. This allows us to examine changes in attention processing independent of motor responses to stimuli. In our 4-week intervention, participants will be randomly assigned to either a meditation group or a music (control) group. Our mediation training will be centered on “focused-attention” (FA) meditation, where participants choose an object or sensation to focus on and monitor for any thoughts or intrusions that distract that focus [22]. Our current study focuses on FA meditation strategies, as it is recommended for beginner-level meditators [23]. FA meditation is recommended for beginners because training one’s mind to be non-judgmental and still for an extended period of time is difficult. Therefore, training to first be able to focus on one thing for an increasing period of time is recommended. Although FA meditation is the first step in a meditation practice, it has been found to increase levels of executive functioning and attention [22, 24].

We hypothesize that 4 weeks of meditation training in older adults will (1) improve attention, as measured by behavioral performance (reaction time and accuracy) on the SART, (2) lead to changes in sensory and cognitive processing of attention-demanding stimuli, as indicated by increases in amplitude and decreases in latency of both the P1 and P300 ERP components, and (3) increase levels of resting state attention, as measured by an increase in individual alpha peak frequency (iAPF) during rest from pre- to post-intervention in only the meditation group. Our work has the potential to increase our knowledge about the relationship between attention, mobility, and electrical brain activity in older adults. Further, our research may be used to inform future studies aimed at improving mobility and reducing falls risk in our aging population.

## Methods

We are conducting a proof-of-concept, 4-week meditation intervention. Our study has received ethics approval from the Health Sciences Research Ethics Board at Western University and our trial is registered at clinicaltrials.gov (ID: NCT03417635), January 30, 2018. The SPIRIT checklist has been completed.

### Participants

We will recruit older adults who meet the following inclusion criteria: (1) living independently in London, Ontario, Canada, (2) completed high school, (3) comfortable writing and reading English, (4) able to walk independently, (5) right-handed (for EEG analysis—left-handed individuals have less lateralized brain structure/function), (6) score > 6/8 on the instrumental activities of daily living scale, and (7) score > 24/30 on the Mini-Mental Status Examination. Participants will be excluded if they (1) have a diagnosis of neurodegenerative disease, (2) have a diagnosis of cognitive impairment (e.g., MCI), (3) have a diagnosis of a psychiatric condition, (4) have had a concussion in the last 12 months, (5) have had a stroke, (6) have musculoskeletal or joint disease, (7) experience dizziness or loss of balance, (8) have visual, auditory, or somatosensory impairment, or (9) have a recent history (past 2 years) of meditation practice or include a meditation component in their religious practice.

Based on our power calculation in g*power, with two groups and setting alpha = 0.05 and assuming a medium effect size [18], we would require a total of 52 participants in our study to obtain a power of 0.8075. Due to 10–15% estimated drop-out, we are aiming to recruit a total of 60 participants or 30 per group.

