### Statistical analysis

Data will be analyzed via SPSS. We will conduct ANOVAs to examine between group (meditation vs. control) differences post-intervention controlling for baseline values for our primary, secondary, and tertiary outcomes. We will covary for relevant variables, including age, sex, and education level, which are known to impact measures of cognitive function. We will use the intent-to-treat model, where all participants will be included in our statistical analyses regardless of whether they completed the intervention or not.

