## Discussion

Our proof-of-concept study has the potential to unveil an affordable, feasible, and scalable intervention to improve attention and mobility in older adults at-risk for falls. While the relationship between attention and falls risk has been examined in numerous cross-sectional studies, research aiming to directly improve attention through an intervention are limited. We acknowledge the potential barriers towards the success of our study which are discussed below.

First, because this study is the first to examine whether meditation training will improve attention in older adults, it is possible that our intervention will not be long enough to observe changes in attention. Because meditation interventions are relatively new in the literature, there is no standardized protocol that has been developed; additionally, research examining the dose-response relationship between meditation and cognitive benefits is lacking. Therefore, our 4-week intervention was chosen based on previous studies that have found medium to large effect sizes for studies between one single session [16] and 2 months [19, 33]. Future studies examining the dose-response relationship between meditation and attention in this particular population are warranted.

Second, we acknowledge that our intervention designed to improve attention in older adults might not translate to changes in mobility and/or a reduction in future falls. However, this will be among the first studies to examine the potential causal role of attention in falls risk—in contrast to the correlational studies that currently dominate the literature. While our current study is not specifically aimed at improving mobility or reducing falls per se, our study provides the groundwork for future definitive RCTs aimed at examining the efficacy of meditation for reducing falls risk in older adults.

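### The sample size sentence calls the effect medium, but 52 participants with power 0.8075 corresponds to a difference of 0.8 SD, conventionally large, for the planned two-group comparison

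*Protocol article*

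**What the plan says.** The Participants section gives the only sample size justification. The calculation was done in G*Power for two groups at alpha 0.05: "assuming a medium effect size [18], we would require a total of 52 participants in our study to obtain a power of 0.8075". The bracketed number is a literature citation. After an allowance of 10–15% for drop-out, "we are aiming to recruit a total of 60 participants or 30 per group". The section gives no numeric effect size, test family, sidedness or correlation.

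The Statistical analysis section fixes the comparison: "We will conduct ANOVAs to examine between group (meditation vs. control) differences post-intervention controlling for baseline values", with age, sex and education as further covariates. That is a post-intervention ANCOVA between two groups. The Discussion justifies the four-week duration by "previous studies that have found medium to large effect sizes".

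**The concern.** The effect label, the N and the power stand in one sentence and should agree. Under the simplest reading (two equal groups, two-sided test, conventional d = 0.5 or f = 0.25 for medium) they do not, and the gap is too large to be rounding.

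The sentence tells readers what the trial can detect. As written, a non-significant result on the Sustained Attention to Response Task could be presented as an 80%-power test of a medium effect. The Discussion offers the study as groundwork for later definitive trials, so the same figures could be carried into their planning.

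**Working it through.** **Inputs.** From Participants: two groups, alpha 0.05, N = 52 (26 per group under equal allocation), power 0.8075, recruitment target 60. From Statistical analysis: between-group post-intervention comparison adjusted for baseline, age, sex and education. Assumptions: two-sided test; medium is d = 0.5 (f = 0.25) and large is d = 0.8 (f = 0.4), since f = d/2 for two equal groups; the covariate-outcome correlation r is not stated and is shown as a range.

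**Formula.** With equal groups the noncentrality is λ = d²N/4. Power is the probability that a noncentral F(1, N − 2, λ) exceeds the 5% critical value. This is the same as the two-sided t-test.

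**Step 1: the plan's own figure.**
- d = 0.8, N = 52: λ = 0.64 × 13 = 8.32, power 0.80749, which rounds to the stated 0.8075.
- d = 0.8, N = 50: λ = 8.00, power 0.791. So 52 is also the smallest balanced N that reaches 0.80.
- Solving backwards, the d that gives 0.8075 at N = 52 is 0.800.
- Drop-out: 52/0.90 = 57.8, so 58; 52/0.85 = 61.2, so 62. The target of 60 lies within that range and is not at issue.

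**Step 2: a conventional medium effect, unadjusted.**
- d = 0.5, N = 52: λ = 0.25 × 13 = 3.25, power 0.424.
- d = 0.5, N = 60: λ = 0.25 × 15 = 3.75, power 0.478.
- d = 0.5, N = 128: λ = 0.25 × 32 = 8.00, power 0.801. N = 126 gives 0.795, so 128 are needed.
- One-sided, d = 0.5, N = 52: power 0.553; N = 102 needed.

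**Step 3: the planned ANCOVA, with d = 0.5 on the raw scale.** Adjustment multiplies the residual variance by 1 − r², so λ = d²N/[4(1 − r²)]. Four covariates leave about 47 residual degrees of freedom.

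| assumed r | λ at N = 52 | power, N = 52 | power, N = 60 | detectable d at 80% power, N = 52 |
|---|---|---|---|---|
| 0 | 3.25 | 0.42 | 0.48 | 0.79 |
| 0.5 | 4.33 | 0.53 | 0.59 | 0.69 |
| 0.6 | 5.08 | 0.60 | 0.66 | 0.635 |
| 0.7 | 6.37 | 0.70 | 0.76 | 0.57 |
| 0.78 | 8.30 | 0.81 | 0.86 | 0.50 |

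The last column is the unadjusted 0.794 multiplied by √(1 − r²), for example 0.794 × 0.866 = 0.69. If f = 0.25 is instead entered on the covariate-adjusted scale, power stays at 0.42.

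**Step 4: other readings of a medium effect.**
- Repeated-measures interaction, f = 0.25, two measurements, correlation 0.5: needs N = 34.
- Repeated-measures between-group factor, same inputs: needs N = 98.
- Regression with f² = 0.15: needs N = 55.

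None gives 52. A repeated-measures interaction at f = 0.20 and correlation 0.5 does: λ = f²Nm/(1 − ρ) = 0.04 × 52 × 2/0.5 = 8.32, hence again 0.80749. In a 2 × 2 design, however, f = 0.20 means a group difference in change of 4 × 0.20 = 0.8 SD.

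**The case against.** The strongest defence is that the inputs are undocumented. The effect size is attributed to a cited study, not declared as d = 0.5. If that study's estimate was near 0.8, the calculation is right and only the adjective is wrong; the Discussion's reference to medium to large effects makes loose labelling plausible. This stands, and it is why the correction should ask for the inputs actually used and not impose them.

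Three stronger conclusions are tempting and should not be drawn.

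- *That the figures can arise only from d = 0.8 (f = 0.4).* The interaction at f = 0.20 gives the same power to every digit, and the third hypothesis in the Background is worded as a pre-to-post change in one group. A medium f = 0.25 interaction would also give about 52 with an untypical, unstated correlation near 0.22. But the f = 0.20 version is still a 0.8 SD difference, f = 0.20 is not the conventional medium value, and an interaction test is not the planned analysis.
- *That the planned analysis has 42% power.* That figure is for the unadjusted test, or for f = 0.25 on the adjusted scale. For a raw d = 0.5, baseline adjustment raises it.
- *That a true medium effect would be missed more often than found.* With r between 0.5 and 0.7 the ANCOVA would miss it in about 30–47% of trials.

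The proof-of-concept label and the Discussion's caution about duration temper the consequences. They do not make a quantitative power statement correct.

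**Conclusion.** The power sentence is wrong as written: either the word medium or the pair 52 and 0.8075 must change. For the between-group comparison the article plans, the pair corresponds to a 0.8 SD difference. A conventional medium effect has about 42% power at N = 52 unadjusted (48% at N = 60), and about 53–70% under ANCOVA for a raw d = 0.5 with r from 0.5 to 0.7. Adjustment reaches 80% only near r = 0.78.

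This rests on a two-sided test, 1:1 allocation and Cohen's conventional values; the correlations are assumptions. Which inputs were entered in G*Power cannot be established from the article. The contradiction does not depend on what the cited study found: an estimate near 0.8 would make the label wrong, and an intended 0.5 would make the figures wrong, unless a high and unstated baseline correlation was assumed.

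**What to change.** Correct the sentence in Participants so that label, N and power agree:

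- State the numeric effect size, the test, its sidedness and any correlation actually used. If the input was d = 0.8, call it large.
- Report power at N = 52 for a medium effect (d = 0.5): about 42% unadjusted and about 53–70% with ANCOVA, naming r = 0.5–0.7 as an assumption.
- Report the detectable difference at 80% power: about d = 0.79 unadjusted and 0.57–0.69 with ANCOVA over the same range.

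A null result will then not be presented as an 80%-power test of a medium effect. Adding that the result will be read as an estimate with a 95% confidence interval would be sensible but is optional. The cost is wording only: the recruitment target and design stay as they are, and the stated power becomes less favourable.

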### Procedure

See Fig. 1 for an overview of our schedule for assessments. We will advertise our study via flyers and posters in the community. Interested participants will be asked to contact us via telephone or email, where we will explain the study in more detail, answer any questions, and screen them for eligibility. If they are eligible and interested in participating, we will schedule an assessment session to obtain informed consent and conduct baseline assessments for demographic, cognitive, and physical measures. They will then be invited to complete a second session for the baseline EEG session. After all baseline measures are obtained, participants will be randomized using a random sequence generator (randomization.com) into one of two groups: meditation training or control. Randomization will be completed on an individual basis regardless of their retirement or community location. Upon completion of the 4-week intervention, all participants will complete the same assessments as baseline (demographic/cognitive/physical measures). All assessments will be completed by a blinded assessor. Baseline testing will occur within 1 month before the first session of the intervention, and the end-point testing will occur within a maximum of 7 days after the last intervention session. Participants will be allowed to discontinue the intervention at any point.

**Fig. 1 Fig1:**
[figure not shown]
Schedule of enrolment, interventions, and assessments

### Intervention

Participants in both groups will complete three 20-min sessions per week in a group setting (6–10 participants) with an experienced meditation leader. The meditations are being led by the graduate student who is carrying out the research. She has had a consistent meditation practice on her own for 3 years and has practiced daily for 1 year. Additionally, she has been teaching weekly meditation sessions for several months. She has experience with various types of meditation, but primarily practices the focused attention meditation type that is being used in this protocol. In addition, they will be encouraged to practice their assigned task (meditation or music listening) during the other 4 days of the week independently. The intervention will last four consecutive weeks (12 in-person sessions total). We will record attendance during each session to measure adherence.

#### Meditation training

Participants will sit in a comfortable position on a chair or on the floor. They will be guided through a focused attention practice that will focus primarily on the sensation of breathing through the nose. As the sessions progress, the practice will become less instructed and more independent with fewer reminders of the task at hand.

#### Music (control)

Participants will sit comfortably in a chair. They will be instructed to close their eyes and relax while listening to an acoustic music track. There will be no further instructions provided to participants in the control group. Music listening was chosen as our control group as it requires the same time commitment and environment as the meditation training but without specifically guiding attention. To date, there is no evidence-based or consistently used control group for meditation research [25]; therefore, we chose a calming music listening group to replicate the possible confounding variables such as socialization, taking the same time out of the day to relax, and others that are expected in the meditation group.

### Descriptive measures

Demographic information (age, sex, and education) will be ascertained via questionnaire. Cognitive status will be assessed using the Mini-Mental Status Examination (MMSE) [26]. Depression will be screened for using the Geriatric Depression Scale (GDS) [27]. Number of comorbidities will be recorded using the Functional Comorbidity Index (FCI) [28]. Instrumental activities of daily living (IADLs) will be assessed using the Lawton and Brody IADL scale [29].

### Primary outcome measure

Our primary outcome measure is behavioral performance on the sustained attention to response task (SART). Participants will view a series of equiprobable but randomly presented digits (0–9) on a computer screen and be required to press a button as quickly and accurately as possible each time a digit is presented, except they will be required to withhold their response for the number “3.” There are 14 blocks, each with 60 trials, which results in a total of 840 trials. Past experiments have used this task in older adults and have shown that this model provides a sufficient number of targets to yield significant between-group differences [9]. Response time and accuracy will be recorded. We will focus on ERPs collected from target trials.

### Secondary outcomes

During performance of the SART task, we will also record electroencephalograms (EEGs) using our Brain Vision 64 channel ActiCHamp. The EEG signal will be recorded using Brain Vision PyCorder (https://www.brainproducts.com/productdetails.php?id=43). EEG activity will be recorded relative to a scalp electrode located over the anterior frontal cortex (AFz) and will be filtered between 0.01 and 100 Hz and digitized at a rate of 500 Hz. We will also record vertical and horizontal electrooculograms to monitor eye movements. ERPs will be analyzed using ERPLAB within Matlab (https://erpinfo.org). Data will be filtered (between 0.1 and 30 Hz), segmented into epochs (− 200 to 800 msec), and cleaned from artifacts (i.e., blinks, movements). Epoched data will then be averaged by event type (target vs. non-target) and then grand averages will be created for each group and time point separately. Our main ERP measures will be mean amplitude and peak latency of the P1 and P300 components, which index sensory and cognitive processing, respectively. These values will be extracted on an individual subject basis and imported into SPSS for further statistical analysis.

We will also use EEG to record 5 min of resting-state (i.e., task-free) electrical signals. For the resting state, participants will sit comfortably with their eyes closed for 5 min. They will be instructed to remain relaxed but awake and to sit as still as possible. We will extract the alpha peak frequency (the maximum power value in the frequency spectrum between 7.5 and 12.5 Hz) for each individual. Resting-state EEG will be analyzed using Fieldtrip within Matlab (http://www.fieldtriptoolbox.org).

